#### 2.10.2. Statistical Analysis

All analyses will be performed based on an intention-to-treat principle to minimise attrition bias. A sensitivity analysis with a per protocol analysis, including, for instance, only the infants and families who have not been transferred from the study site to another hospital before discharge home, will also be performed. Possible bias due to differential withdrawal or study drop-out will be assessed in this per protocol sensitivity analysis as well. We will consider performing a subgroup analysis based on clinical characteristics, to adjust for differences in (severity of) infants’ medical conditions.

Baseline characteristics of the intervention and control group will be compared using student *t*-tests for continuous normally distributed variables, and Chi-square tests for categorical variables. Non-parametric tests will be used for variables that do not follow a normal distribution. Missing data will be handled by multiple imputation chain equations (mice) [70] with adjustment for clustering [71]. Rubin’s rules will be applied to pool the results of the different imputed dataset [72]. As described and proposed by the Panel on Handling Missing Data in Clinical Trials, we will carry out sensitivity analyses with different missing data strategies adjusted for clustering [73]. We will consider missing completely at random, missing at random, and missing not at random approaches.

With a generalised linear mixed modelling (GLMM) analysis, we will analyse whether parental stress at discharge is decreased after the intervention. We will include the factor “cluster” (hospital) as random effects, and “step” will be included as fixed (time) effect. In a secondary analysis, adjustment can be applied for possible confounders, such as (medical) characteristics of the infant during hospital stay. Adjustment for possible time effects will be made.

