### 2.2. Design

Due to the nature of the intervention, which involves changes to unit-level provision of care (medical rounds) and interaction between participants, there is a risk of cross-contamination. Therefore, to avoid contamination of patients and staff, the stepped-wedge cluster-randomised controlled trial design was selected. The trial is designed according to the CONSORT 2010 guidelines for stepped-wedge cluster-randomised controlled trials [28]. Randomisation will be performed using a random number generator, which will randomly assign the timing of start of intervention between sites. Hospitals will be stratified by level of care delivered (post-intensive care or not). The program will generate a series of blocks of varying sizes for each stratum and allocate units a time for intervention (3, 6, 9, 12 or 15 months, respectively) as is visualised in Figure 1.

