### 2.10. Statistical Procedures

#### 2.10.1. Sample Size Calculation

Based on previous research, a mean difference of 13 points (0.5 standard deviations) on the total score of the PSS:NICU is expected between the intervention and control groups after implementation of FCR and FICare [25,26]. The stepped-wedge design will have a total of 7 steps of 3 months each. At each step, two hospitals will implement the FICare intervention. One step will be an implementation (or wash-out) period. With an expected amount of 25% missing data, a power of 80%, intra-cluster correlation of 0.01 and an eta of 0.5 times the estimated effect, we aim to include 600 infants and their parents divided over 10 clusters.

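### The primary model has only a ward intercept and a fixed step, so its standard error is too small if within-ward correlation decays between quarters or the intervention effect varies between wards, as the plan itself expects

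*Protocol article*

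**What the plan says.** Section 2.10.2 (Statistical Analysis) gives the model class and aim: "With a generalised linear mixed modelling (GLMM) analysis, we will analyse whether parental stress at discharge is decreased after the intervention". It then names the terms: "We will include the factor “cluster” (hospital) as random effects, and “step” will be included as fixed (time) effect". One more sentence bears on time: "Adjustment for possible time effects will be made". It does not say which time effects, or whether they may differ between wards.

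Section 2.10.1 (Sample Size Calculation) expects "a mean difference of 13 points (0.5 standard deviations) on the total score of the PSS:NICU" and uses an "intra-cluster correlation of 0.01 and an eta of 0.5 times the estimated effect". The article does not define eta. In stepped-wedge sample size work it usually denotes between-ward variation of the intervention effect, and it is read that way here.

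The Discussion (section 4) says that hospitals may differ in how well they carry out the intervention, and that time interaction is taken into account in the analysis. No such interaction appears among the terms in 2.10.2.

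**The concern.** A model with one random intercept per ward and common step effects makes two assumptions. Two families on the same ward are equally correlated whether they are admitted in the same quarter or more than a year apart. The intervention also works equally well on every ward.

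In a stepped-wedge trial most of the information on the effect comes from comparing quarters within a ward. If wards drift individually between quarters (staffing, occupancy, local policy), part of that drift adds error to the effect estimate that the model does not count. If the effect differs between wards, ten wards are a small sample of effects, and that uncertainty is not counted either. The result would be a confidence interval for the primary outcome that is too narrow and a p-value that is too small.

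The second assumption also conflicts with the plan's own sample size inputs: eta enters the calculation of N but has no counterpart in the stated analysis.

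**Working it through.** **Inputs from the article.** Effect 13 points = 0.5 SD, so SD = 13/0.5 = 26 and the total variance is 676. ICC 0.01. Eta = 0.5 × 13 = 6.5. Ten wards, two per step, seven three-month periods, one implementation quarter per ward. 600 families, 25% missing.

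**Assumptions.** Two-sided alpha 0.05 (not stated). Implementation quarter left out. One score per family. Equal ward-quarter sizes: 600 × 0.75 = 450 analysed over 10 × 6 = 60 ward-quarters, or 7.5 each. The cluster autocorrelation (CAC), i.e. the correlation between quarters divided by that within a quarter, is not given; values of 1, 0.8 and 0.5 were tried. ICC 0.05 and 0.10 are also assumed.

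**Formula.** For ward-quarter means, the covariance matrix of ward i is

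V_i = (σ²/n + ω²)·I + τ²·J + η²·x_i x_iᵀ,

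with τ² + ω² = ICC × 676, σ² = 676 − τ² − ω², CAC = τ²/(τ² + ω²), and x_i the ward's 0/1 intervention indicator. The SE of the effect is the square root of its diagonal element in (Σ Z_iᵀ V_i⁻¹ Z_i)⁻¹, where Z_i holds the step and intervention columns. The stated analysis sets ω² = 0 and η = 0.

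**The plan's own figure.** With ICC 0.01, τ² = 6.76.
- Eta as a variance of 6.5 (SD √6.5 = 2.55): 446 families for 80% power; 446/0.75 = 595, close to 600.
- Eta as an SD of 6.5: 588 families; 588/0.75 = 784. This matches 600 only if the 25% inflation is left out. Power with 450 analysed is then 72%.
- No heterogeneity: SE 4.50 with 450 analysed; power = Φ(13/4.50 − 1.96) = Φ(0.93) = 82%.

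So N = 600 is reproducible, but the reading of eta decides how.

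**Hand check on heterogeneity.** Without it, the smallest possible variance of the effect estimate is 4.50² = 20.25. Ward-specific effects with SD 6.5 add 6.5² × Σw_i², where the ward weights w_i sum to 1, so at least 6.5²/10 = 4.23. The SE is then at least √(20.25 + 4.23) = 4.95, or 10% above 4.50. The full formula gives 5.12.

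**Simulation of the stated model** (40,000 trials per row, REML, Wald z, no true effect):

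| ICC | CAC | SD of ward effects | True SE | Model SE | Type I error |
|---|---|---|---|---|---|
| 0.01 | 1 | 0 | 4.55 | 4.47 | 5.5% |
| 0.01 | 0.8 | 0 | 4.54 | 4.45 | 5.6% |
| 0.01 | 0.5 | 0 | 4.52 | 4.42 | 5.6% |
| 0.01 | 0.8 | 6.5 | 5.26 | 4.70 | 8.3% |
| 0.05 | 1 | 0 | 4.91 | 4.77 | 6.0% |
| 0.05 | 0.8 | 0 | 5.00 | 4.73 | 6.5% |
| 0.05 | 0.5 | 0 | 5.11 | 4.65 | 7.6% |
| 0.05 | 0.8 | 6.5 | 5.52 | 4.86 | 8.6% |
| 0.10 | 1 | 0 | 4.99 | 4.84 | 5.8% |
| 0.10 | 0.8 | 0 | 5.28 | 4.83 | 7.5% |
| 0.10 | 0.5 | 0 | 5.65 | 4.79 | 9.7% |

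As a check on the fourth row, a reported SE of 4.70 against a true 5.26 turns the 1.96 cut-off into 1.96 × 4.70/5.26 = 1.75, a two-sided error of about 8%. Separate, smaller simulations agree with the table to within about one percentage point.

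If eta is a variance of 6.5, a smaller simulation gave 5.1% at ICC 0.01 and 6.8% at ICC 0.05, so heterogeneity of that size adds little.

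**With a random ward-by-quarter effect added** (t reference on 60 − 7 − 1 − 9 = 43 df), type I error is about 4-6% without effect heterogeneity. With ward effects of SD 6.5 it is about 6-7%, so this term alone removes only part of that error.

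**The case against.** The strongest reply is that the only ICC in the article is 0.01, where the stated model is nearly right unless effects vary. The larger figures need ICC and autocorrelation values that the article does not supply. That stands, and those figures are shown as assumptions. It does not remove the point, because the heterogeneity case uses the plan's own eta.

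A second reply is that a condensed article need not list every term: it speaks of random effects in the plural, promises adjustment for time effects, and mentions time interaction in the Discussion. This leaves slight room. But the plural is attached to the single factor hospital, and neither time statement names a ward-specific term. The terms as stated are what would be fitted.

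Some stronger readings are tempting but not supported:
- *The interval is too narrow unless the ICC really is 0.01.* This fails both ways. With no decay, ICC 0.05-0.10 gives only about 6%. ICC 0.01 does not protect the model if eta is an SD of 6.5.
- *Type I error as high as 14%.* This needs about 17 scores per ward-quarter from both parents, with no term for the family, as well as assumed ICC and autocorrelation values. At ICC 0.01 the same cell size gives about 6%.
- *A small-sample correction for ten wards is missing.* Such a correction is commonly left to the SAP, which is not shown. Using z costs about 0.5-1 percentage point when the model is right.
- *The randomisation stratum is missing from the model.* Section 2.2 does stratify by level of care, but the stratum is constant within a ward, so it should barely affect an effect estimated mostly within wards.

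**Conclusion.** The concern holds in a limited form. The stated primary model understates the standard error if within-ward correlation decays between quarters or the intervention effect varies between wards, and the plan anticipates the second.

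The size depends on what is true. At the documented ICC with no heterogeneity it is minor, at 5-6%. With eta as an SD of 6.5 it is about 8%, the model SE being about 11% too small (4.70/5.26 = 0.89). Under assumed values it is about 6.5-8% (ICC 0.05, CAC 0.8-0.5) or 7.5-10% (ICC 0.10). If eta is a variance of 6.5, its own contribution is small. The article does not settle which reading applies; the reproduced sample size with inflation favours the variance, while eta is more usually an SD.

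These figures rest on two-sided 5%, equal cells and one score per family. Ward volumes of 80 to 300 per year (section 2.3) mean that real cells will be unequal. The point is a cheap improvement; it does not invalidate the design.

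**What to change.** 1. Add a random ward-by-step effect to the primary model, beside the random ward effect, fixed step and intervention.
2. State in 2.10.1 whether eta is a standard deviation or a variance, and of what.
3. Add a ward-specific random intervention effect that matches eta, in the primary model or in a prespecified sensitivity analysis.
4. Keep the current model as a sensitivity analysis.
5. Recheck N = 600 under the stated meaning of eta.

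**Cost.** One or two model terms. The ward-by-step effect makes the reported SE about 3-7% larger at ICC 0.01-0.05. If eta is an SD of 6.5, a model that allows for it has an SE of about 5.1 and power of about 72% with 450 analysed, against 82% with no heterogeneity. That loss comes from the heterogeneity; the stated model would only hide it.

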#### 2.4.1. Inclusion Criteria

Recruited patients will be patients admitted to a level 2 neonatal ward for 7 days or more. To be eligible to participate in this study, a subject (parent–infant dyad/triad) must meet all of the following criteria:−Infant requiring hospital admission directly (within 24 h) after birth;−Parent are 18 years or older;−Written, informed consent of both parents/legal guardians (compliant to the regulations of the Central Committee on Research Involving Human Subjects).

All healthcare professionals (nurses, nurse practitioners, residents, paediatricians and neonatologists) that are employed on the neonatal ward during the study are eligible to participate regarding healthcare professional outcomes.

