#### 2.9.1. Infant Outcomes

Infant outcomes include length of hospital stay, breastfeeding rates, growth, neurodevelopment at the (corrected) age of 12 months and saliva cortisol and buccal mucosal cells (see Section 2.9.5).

Neurodevelopment will be assessed using the Ages and Stages Questionnaire (ASQ, 3rd edition) [33]. With this tool, infant development can be assessed as reported by parents. The ASQ has been validated in a comparable population [34], and the validated Dutch version will be used for Dutch speaking participants [35]. The ASQ encompasses 5 domains: communicative, gross motor, fine motor, problem solving and adaptive skills. Each domain consists of 6 questions regarding the milestones that fit the age of the infant. Parents respond to the different items with “yes” (score = 10), “sometimes” (score = 5) or “not yet” (score = 0). For each domain, the score of the six items is summed, resulting in a domain score ranging from 0 to 60 and a total ASQ score with a maximum of 300 points. A positive screening is defined as scoring >2SD below the mean of the Dutch reference population in one domain, or scoring >1SD below the mean on more than one domain.

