#### 2.9.2. Parental Outcomes

At discharge, parents’ experiences of the hospital admission will be evaluated in several domains. Their experience of shared decision-making will be measured by means of the Shared Decision Making Questionnaire (SDM-Q-9). This questionnaire contains 9 items, with a unidimensional structure, regarding patients’ experiences of the process of decision-making [36]. To adjust the SDM-Q-9 to a paediatric setting, “my doctor” will be replaced by “my baby’s doctor” and “my medical condition” will be changed to “my baby’s medical condition” with permission of the original authors. The SDM-Q-9 shows a good validity and reliability, with a Cronbach’s a of 0.94. Validation of the Dutch translation are in the same range, providing good reliability [37]. To be able to adjust for the preference parents may have in being involved in decision-making, the Control Preferences Scale (CPS) will be used. The CPS was originally created as a card-sorting exercise to assess the preferences an individual may have regarding the control in medical decision-making [38]. The CPS will be used in the form of a one-item questionnaire [39]. The item is answered on a 5-point Likert scale, and parents will be asked to fill out the CPS at discharge.

The CO-PARTNER tool will measure parental participation in the neonatal care and collaboration of parents with the medical team [40]. This tool can be used on the neonatal ward to describe the culture of a unit, measure the amount of FICare applied, define what parents can do in the care of their infant and in which care activities they collaborate with healthcare staff. It consists of 31 items within 6 domains: daily care (11 items), medical care (4 items), gathering information (3 items), advocacy (3 items), time spent with the infant (3 items) and closeness and comforting of the infant (7 items). Internal consistency of the domains varies from 0.558 to 0.938 and has a good convergent and divergent validity [40].

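### The optional secondary adjustment and the planned adjustment for decision preference use variables recorded after ward exposure began, so the adjusted estimates may not be total effects of FICare

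*Protocol article*

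**What the plan says.** Three statements in the protocol article bear on this.

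- **Secondary adjusted model (2.10.2).** The main model has hospital as a random effect, and step "will be included as fixed (time) effect". The article then adds that in a secondary analysis "adjustment can be applied for possible confounders, such as (medical) characteristics of the infant during hospital stay". It gives no other example.
- **Decision preference (2.9.2).** "To be able to adjust for the preference parents may have in being involved in decision-making, the Control Preferences Scale (CPS) will be used". The scale is described alongside the SDM-Q-9. On timing, "parents will be asked to fill out the CPS at discharge", and Table 1 lists it at no other visit.
- **Subgroups (2.10.2).** "We will consider performing a subgroup analysis based on clinical characteristics, to adjust for differences in" the infants' medical conditions and their severity.

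Two further places matter. Section 2.9.1 states: "Infant outcomes include length of hospital stay, breastfeeding rates, growth". Section 2.4.1 requires: "Infant requiring hospital admission directly (within 24 h) after birth".

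**The concern.** A confounder must not be a consequence of the exposure. Infants enter hospital within a day of birth. Apart from time in a level 3 unit before transfer, what happens to them during the stay happens under whichever care model the ward is running. The article calls such characteristics confounders and sets no limit to those that precede exposure.

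If a covariate lies on the path from FICare to parental stress, the adjusted estimate leaves out the part of the effect that runs through it. If the covariate also shares unmeasured causes with stress, conditioning on it adds a bias that may go either way. The CPS raises the same question for the SDM-Q-9.

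What is at stake is interpretation. This is an unblinded trial with ten clusters and individual consent. If case mix differs between control and intervention periods, readers will turn to the adjusted result and take it as the confounder-corrected effect of FICare. As worded, it may not be that.

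**Working it through.** **Step 1: does each adjuster follow exposure, and could FICare change it?**

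| Adjuster | When recorded | Sign in the article that FICare may change it |
|---|---|---|
| Infant characteristics in the stay | After birth and admission (2.4.1, 2.10.2) | Length of stay, breastfeeding and growth are outcomes (2.9.1); the package includes skin-to-skin and milk-expression facilities (2.5) |
| CPS | Discharge only (2.9.2, Table 1) | Parents take part in rounds and in shared decisions, with support and education for that role (2.7) |

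The onward path from the infant's course to the primary outcome is plausible: 14 of the 26 PSS:NICU items concern the infant's appearance (2.8).

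**Step 2: what adjustment would do.** The plan states no adjusted effect to reproduce. The only figures taken from it are in 2.10.1: 13 points equals 0.5 SD, so SD = 13 / 0.5 = 26 points. All other inputs below are assumptions. The sketch leaves out clustering and step.

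Let X = 1 under FICare, M the in-stay covariate (SD 1 within group), U an unmeasured common cause (SD 1) and Y the stress score:

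- M = −aX + cU + error
- Y = −δX + bM + dU + error
- Total effect of X on Y: −(δ + ab)
- Coefficient of X after adjusting for M: −δ + acd, because the mean of U given X and M is c(M + aX)

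**(i) Mediation only (c = d = 0).** The adjusted reduction is 13 − ab. Take a from 0.1 to 0.5 SD and b from 2.6 to 7.8 points per SD (0.1 to 0.3 of 26).

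- Smallest loss: 0.1 × 2.6 = 0.26, leaving 12.74 points (2% removed).
- Middle case: 0.5 × 5.2 = 2.6, leaving 10.4 points (20% removed).
- Largest loss: 0.5 × 7.8 = 3.9, leaving 9.1 points (30% removed).

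**(ii) Mediation plus a common cause.** With δ = 10.4, a = 0.5, b = 5.2, c = 0.5 and d = 10.4, the total reduction is 10.4 + 2.6 = 13.0. The adjusted reduction is 10.4 − 0.5 × 0.5 × 10.4 = 7.8. Simulation gave 7.80.

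**(iii) No true effect, common cause present.** With δ = b = 0 and a, c, d as in (ii), the total is 0, but the adjusted coefficient is 0.5 × 0.5 × 10.4 = +2.6 points. Simulation gave 2.59. If d is negative, the formula gives −2.6, so the sign can go either way.

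**(iv) Covariate not changed by FICare (a = 0).** The adjusted reduction stays at 13.0. Simulation gave 13.00.

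The same algebra applies to the SDM-Q-9 adjusted for CPS. No figures are given there, because the article states neither an expected difference nor an SD for that scale.

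**Step 3: subgroups.** Estimates within severity strata can control for severity if they are pooled. A subgroup analysis, however, asks whether the effect differs between strata. If the strata are formed from the in-stay course, the problem in Step 2 returns.

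**The case against.** The best defence has four parts.

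- **Scope.** The main model carries no post-exposure covariate, and the infant adjustment is both secondary and optional. This stands. A reader might infer that the primary estimate is compromised; the article does not support that.
- **Which characteristics.** The article does not say that length of stay, feeding or growth will be covariates. Medical characteristics may include diagnosis, gestational age or complications of an earlier level 3 stay, all of which precede exposure on the study ward. The discussion also notes that studies disagree on FICare's effect on length of stay. This stands too. It is therefore too strong to call the covariates mediators outright, or to say that adjustment will remove part of the effect. The criticism is that the wording admits affected variables and calls them confounders.
- **Detail belongs in the analysis plan.** A closed covariate list does, and its absence is no fault here. The choice of in-stay characteristics as the example, and of discharge as the only CPS time point, is stated in the article itself.
- **The CPS.** It concerns a secondary outcome, 2.10.2 specifies no CPS-adjusted model, and the shared decision-making modules in 2.5 are for professionals. A shift in parents' preference is possible, not shown. Even so, 2.9.2 gives adjustment as the reason for collecting the scale, and one discharge measurement cannot show whether preference has moved.

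The aim behind the adjustment, dealing with case-mix differences between periods, is legitimate. Variables fixed before exposure serve it without this risk.

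**Conclusion.** The point holds in a conditional and limited form. Both named adjusters are recorded after ward exposure began, and the article gives reason to think that FICare could alter them. An adjusted estimate built on them can therefore differ from the total effect, in either direction. The primary analysis is unaffected.

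The size cannot be derived from the documents. The 2% to 30% loss, the 7.8-point result and the spurious 2.6 points rest wholly on assumed values of a, b, c and d, and the loss is zero where FICare leaves the covariate unchanged. A reader might be tempted to attach a definite share to the loss, say 20% to 40% of 13 points (leaving 10.4 to 7.8). No statement in the article supports such a range.

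On subgroups the fault is one of description: stratification can control for severity, but a subgroup analysis should not be presented as adjusting the overall effect. The change is worth making because it costs almost nothing and protects the reading of the adjusted results.

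**What to change.** 1. **Section 2.10.2, adjusted model.** Limit the secondary adjusted model to prespecified variables fixed before exposure on the study ward: for example gestational age, birth weight and, where recorded, multiple birth and prior NICU stay. The cut-off should be the start of ward exposure, not inclusion. Eligibility needs a stay of at least 7 days and the article gives no inclusion date, so a variable recorded before inclusion may already follow exposure.
2. **Models with in-stay variables.** Label them exploratory or mediation analyses.
3. **SDM-Q-9.** Report it without CPS adjustment as the main result, show CPS descriptively by period, and mark any CPS-adjusted result as exploratory.
4. **Subgroups.** Define them on pre-exposure characteristics, test them by interaction, and drop the description as adjustment.

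**Cost.** This is mainly wording. Infant baseline characteristics appear in Table 1, and gestational age must be known to apply its footnotes and to compute corrected age. The article does not itemise the other variables, and footnote 1 limits admission measurement to infants born before 35 weeks, so availability should be checked. The one statistical drawback is that pre-exposure variables may capture less of the severity difference between periods.
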